#### 5.4.3 Functional performance assessment

Three functional tests, which simulate activities of daily living will be performed. During the three tests, the individuals will be standing with their arms at their sides and will start each of the tests with their arms at their sides and their hands on the side of their thighs.

1. Reach a point above the head: the individuals will be positioned 30 cm away from a wall, which will have a target 10% higher than the individual's height. During the test, subjects will repeatedly reach the target point on the wall, perform a sagittal arm raise, and return to the starting position.

2. Reach Back of Head: Subjects will reach the back of head (occipital region) and return to starting position. Subjects will not be allowed to tilt the trunk or head during the test and the elbow must be aligned laterally with the head while subjects will touch the occipital region.

3. Reaching for the opposite shoulder blade or back: Subjects will reach for their opposite shoulder blade, or attempt to reach a point farther behind their back, and return to the starting position. Subjects will not be allowed to tilt or rotate their trunk or head during the test.

Each of the tests will be performed 20 times and as quickly as possible, once on each side. The time to complete the task will be measured with a stopwatch.

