**2019**

## ABSTRACT

The aim of this project is to characterize the effects of two types of exercise – isometric versus isotonic – on shoulder pain and function and the relationship with neuromuscular control in individuals with rotator cuff (RC) tendinopathy. Forty-six individuals (18-60 years old) with shoulder pain (>3 months) and proven unilateral tendinopathy in the supraspinatus and/or infraspinatus by means of ultrasound or magnetic resonance imaging will participate in this study. Subjects will be randomly allocated to one of two exercise groups: isometric and isotonic. They will be evaluated before and after the first treatment session, and again after six weeks of treatment. The outcomes to be evaluated are: a) pain and general shoulder function, using the Penn Shoulder Score and The Western Ontario Rotator Cuff Index questionnaire; b) neuromuscular control through the electromyographic activity of the trapezius (lower portion), serratus anterior, deltoid (middle portion), and infraspinatus, during maximal isometric contractions of shoulder elevation at 90°, internal and external rotation of the shoulder at 0° of arm elevation and during elevation of the arm at 30, 60, 90 and 120 degrees with and without load using a surface electromyographic signal recording system (EMG system do Brazil®); we will evaluate the amplitude of muscular activity of each muscle and the ratio between muscle pairs: 1) infraspinatus and middle deltoid; 2) infraspinatus and lower trapezius; and 3) lower trapezius and serratus anterior; and c) functional performance through tests that simulate activities of daily living, which include: reaching a point above the head; reach the back of the head; and reaching the back or the opposite scapula, where the performance time and levels of pain and effort will be evaluated. The two groups will undergo a protocol of stretching and strengthening of the periscapular musculature. The isometric group will perform additional exercises for the RC, with 3 repetitions of 32s at 70% of the maximum isometric force for each exercise. The isotonic group will perform exercises for RC in a concentric and eccentric way, with 3 sets of 8 repetitions for each exercise at 8 RM. The exercise load of the two groups will be adjusted in weeks 3 and 5 of the six-week protocol. Treatment effects between groups will be evaluated using two-way ANOVAs with repeated measures, with the aid of the Statistical Package for the Social Sciences (SPSS) software. The results of this study will contribute to knowledge in the field of assessment and rehabilitation of the shoulder complex and may support decision-making process for treating RC tendinopathy.

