#### 5.4 Evaluation procedures

All included individuals will undergo the following assessments: a) pain and general function of the shoulder complex; b) electromyographic activity of the shoulder complex musculature during maximal isometric contractions; and c) electromyographic activity of the shoulder complex muscles during arm elevation in the scapula plane.

This evaluation sequence will be carried out in three moments: 1) initial evaluation, immediately before the first intervention session; 2) immediately after the first exercise session; and 3) after six weeks of intervention. All evaluations will be carried out by an evaluator who will not know which intervention group the individuals belong to (blind evaluator), with the interventions applied by two other trained researchers.

One week before the initial assessment, individuals will be randomly allocated using the online randomization tool for randomized clinical trials, available on the website ([www.randomization.com](http://www.randomization.com)). To guarantee the confidentiality of the allocation of individuals, this will be carried out by one of those responsible for applying the intervention, who will be the only one to know which group the individuals belong to. After determining the group, individuals will be introduced to the evaluation process and equipment, and will undergo a test to determine the elastic band to be used during periscapular muscle strengthening exercises. In addition, individuals allocated to the isometric or isotonic exercise group will perform the initial load determination test for each of the exercises. The sequences of the study procedures are described in Figure 1.

[figure not shown]

**Figure 1.** Study's flowchart.

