Active surface electrodes composed of an Ag/AgCl system associated with a conductive gel, simple differential, of bipolar configuration with dimensions of 4 cm X 2.2 cm of adhesive area and 1 cm of conductive area separated by 2 cm between electrode will be used (Miotec®, Brazil). A reference electrode of monopolar configuration will also be used, composed of an Ag/AgCl system associated with a conductive gel, with a diameter of 3.8 cm of adhesive area and 1 cm of conductive area (Miotec®, USA).

The positioning of sensors for the evaluation of lower trapezius, serratus anterior, middle deltoid and infraspinatus will follow the procedure described in

Michener et al. (46). A reference electrode will be attached to the ulnar styloid process on the contralateral side (48). Before placing the electrodes, the skin of the assessed regions will be shaved and cleaned with alcohol. The electromyographic activity will be evaluated only in the muscles of the symptomatic side, and after the tests, the individuals will be questioned about their pain, using the Numerical Pain Rating Scale (0-10, with 0 being no pain and 10 being the worst possible pain). (49).

To evaluate the amplitude of the electromyographic signal of each muscle and subsequently measure the muscle activation ratio between muscle pairs, the raw data will be filtered at a bandpass frequency of 20-450 Hz, rectified and smoothed using an algorithm of root mean square (RMS) with a 50-millisecond moving window, using Matlab software.

The ratio of muscle activation between the following pairs will be evaluated: 1) infraspinatus and middle deltoid; 2) infraspinatus and lower trapezius; and 3) lower trapezius and serratus anterior. These muscle pairs were selected since individuals with RC dysfunction have increased compensatory activity of the middle portion of the deltoid (14–16) and incoordination between the lower trapezius and serratus anterior and between the upper and lower portions of the trapezius (13).

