### 5.5 Intervention Protocol

Individuals from each group will perform an exercise session according to their group (isometric and isotonic) on the day of baseline assessment in order to verify the immediate effects of exercises. Then, they will participate in a six-week intervention, twice a week, in order to verify the effects of a strengthening program directed at the RC. Exercises will be performed on both limbs.

Individuals from all groups will undergo a protocol for stretching and strengthening the periscapular musculature following the protocol used by Camargo et al (53), which consists of stretching the upper trapezius and pectoralis minor muscles and the posterior portion of the shoulder, and strengthening the serratus anterior and lower trapezius muscles.

The evaluation to determine the initial loads of the exercises will be carried out one week before the baseline evaluation and beginning of the interventions. At that moment, participants will also familiarize themselves with each exercise with light resistance and will be guided by the evaluator to perform the technique correctly. In order to adjust and progress the exercise load over the six weeks of intervention, the assessments will be repeated in the third and fifth weeks of intervention, as shown in Figure 2 with the flowchart of the intervention procedures and progression of each group.

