## 5.7 Statistical analysis

Data will be analyzed statistically in a descriptive and inferential way. Mean and standard deviation will be calculated for all demographics and dependent variables. Regarding inferential analyses, initially, the Shapiro-Wilk Normality Test will be used to classify the distribution of each variable.

In order to perform the comparison between the two groups (isometric and isotonic) and between the evaluations, for each dependent variable, we will apply two-way ANOVA with repeated measures when the data are considered parametric and Friedman when the data are non-parametric.

When necessary, post hoc Tukey or Duncan tests will be applied, respectively. All tests will be performed using the Statistical Package for Social Sciences – SPSS, version 20.0 software, and the significance level adopted will be  $\alpha \leq 0,05$ .

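### Functional tests are timed on both sides, but the plan does not say which side is analysed and adjusts for no baseline; ANCOVA on the baseline times already collected would be a cheap gain

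*Combined protocol and SAP*

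**What the plan says.** Section 5.4.3 describes three timed reaching tests: "Each of the tests will be performed 20 times and as quickly as possible, once on each side". The measure is completion time: "The time to complete the task will be measured with a stopwatch". The abstract adds pain and effort ratings, which this point does not cover.

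The abstract describes participants as having "proven unilateral tendinopathy in the supraspinatus and/or infraspinatus by means of ultrasound or magnetic resonance imaging", so each participant has one side without the diagnosed disease. Section 5.5 states: "Exercises will be performed on both limbs". The healthy side is therefore trained with the assigned programme.

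For electromyography the side is fixed in section 5.4.2: "The electromyographic activity will be evaluated only in the muscles of the symptomatic side". Section 5.4.3 has no matching sentence for the functional times.

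Section 5.7 says that "we will apply two-way ANOVA with repeated measures when the data are considered parametric and Friedman when the data are non-parametric". It names no covariate and does not mention side.

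Section 5.4 sets the evaluations as "1) initial evaluation, immediately before the first intervention session; 2) immediately after the first exercise session; and 3) after six weeks of intervention". Its list of assessments leaves out the functional tests, so their schedule rests on the abstract, which places them among the outcomes measured at the same three times.

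**The concern.** Three tests on two sides give six times per participant per evaluation, and nothing says which of them make up the functional outcome. The protocol fixes the side for electromyography but not here, so the choice is left to whoever analyses the data.

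The second issue is precision. Baseline times on both sides are collected before the first session. The planned group-by-time test uses the symptomatic side's baseline only by differencing, and it does not use the healthy side's baseline at all. Differencing gives the baseline a weight of one. ANCOVA estimates the weight, and its residual variance is no larger. The healthy-side baseline could add to this because it reflects a person's general speed and effort without the slowing due to pain. With about 21 completers per group, a smaller standard error is worth having if it needs no new data.

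**Working it through.** **The plan's own figure.** There is no sample-size calculation for functional time. The only one, in section 5.2, is for pain on arm elevation: difference 2.05, SD 2.30, 80% power, alpha 0.05. The two-sided t-test calculation gives 20.77, so 21 per group (power 0.805), which agrees with the plan. I use 2 × 21 = 42 completers below only to price degrees of freedom.

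**Model (assumed; the documents give no SD or correlation for these times).** Time = person speed + pain slow-down + error.
- Speed variance is 1 on each side, with between-side speed correlation c = 0.5, 0.8 or 1.0.
- Slow-down variance on the symptomatic side is S0 = 0.3 to 1.0 at baseline. At week 6, S6 is equal to S0 or half of it. The correlation between visits is r = 0.3 to 0.7.
- Error variance is E = 0.1 to 0.4.

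**Formulas.** Let V0 = 1 + S0 + E, V6 = 1 + S6 + E, VH = 1 + E and C = 1 + r√(S0·S6). The healthy-side baseline has covariance c with both symptomatic-side times.
- Change contrast: V0 + V6 − 2C.
- ANCOVA on own baseline: V6 − C²/V0.
- ANCOVA on both baselines: the line above minus [c(1 − C/V0)]² / (VH − c²/V0).
- Cost of k covariates in variance: 1 + k/(42 − k − 3), which is 1.0263 for k = 1 and 1.0541 for k = 2.

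**Middle case by hand** (S0 = S6 = 0.5, E = 0.2, r = 0.5, c = 1). V0 = V6 = 1.7, VH = 1.2, C = 1.25.
- Change: 3.4 − 2.5 = 0.900.
- Own baseline: 1.7 − 1.5625/1.7 = 0.781.
- Both: 0.781 − 0.2647²/0.6118 = 0.666.
- SE of both against change: √(0.666 × 1.0541/0.900) = 0.883.

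| Setting | Change | Own | Both | SE own/change | SE both/change | SE both/own |
|---|---|---|---|---|---|---|
| S0 = 1.0, S6 = 0.5, E = 0.1, r = 0.3, c = 1 | 1.276 | 0.900 | 0.614 | 0.851 | 0.712 | 0.837 |
| Middle case, c = 1 | 0.900 | 0.781 | 0.666 | 0.944 | 0.883 | 0.936 |
| Middle case, c = 0.5 | 0.900 | 0.781 | 0.764 | 0.944 | 0.946 | 1.003 |
| S0 = S6 = 0.3, E = 0.1, r = 0.7, c = 0.5 | 0.380 | 0.354 | 0.349 | 0.978 | 0.984 | 1.006 |

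Over the whole grid the SE ratios are:
- own baseline against change: 0.84 to 0.98;
- both baselines against change: 0.71 to 0.98;
- both baselines against own baseline: 0.82 to 1.01.

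**Cross-check with correlations set directly.** The symptomatic-side baseline-to-week-6 correlation runs from 0.5 to 0.9, and the healthy-side baseline has equal correlations of 0.3 to 0.7 with both symptomatic-side times. Own-baseline ANCOVA against change is 0.88, 0.93 and 0.99 at correlations of 0.5, 0.7 and 0.9. Both baselines against change is 0.73 to 1.00. The further factor from the healthy side is 0.84 to 1.01. It breaks even at a partial correlation of about 0.16. At zero partial correlation it costs √(1.0541/1.0263) = 1.013, or 1.3%.

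**Healthy-side baseline added to the planned change contrast.** Its covariance with the change is c − c = 0, so the variance reduction is zero. It reaches 4% to 20% only if its two correlations differ by 0.2.

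**The case against.** The strongest objection is that the planned group-by-time contrast is within-person, so stable speed already cancels from it. This stands: under the model, adding the healthy-side baseline to that contrast gains nothing. The case therefore rests on moving to ANCOVA with the own baseline, and the healthy side is a supplement to that.

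The supplement is also uncertain. If dominance or side-specific ability lowers the between-side speed correlation to 0.5, the healthy-side covariate gains about nothing and may cost slightly. That stands too, but the loss is about 1% in standard error.

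Two stronger readings are tempting. A reader might infer that healthy-side times are planned as further outcomes, because section 5.7 covers each dependent variable. The plan never lists them as dependent variables; it gives them no role. A reader might also fear that the sides will be averaged or expressed as a ratio. No section proposes either, so a power loss from doing so is not a property of this plan.

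The baseline is also not strictly pre-randomisation. Sections 5.4 and 5.5 place allocation, load testing and exercise familiarisation one week earlier. It does precede the first session and is taken by a blinded evaluator, and the planned contrast depends on the same own-side baseline. Finally, the Friedman alternative cannot carry covariates.

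**Conclusion.** The point holds as a cheap improvement to a non-primary outcome. The missing side is a gap in definition that one sentence closes. The change of method is the substantive part.

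Under the assumed variance components, ANCOVA on both baselines gives a standard error 0.71 to 0.98 of that from the planned baseline-to-week-6 contrast. In the two middle cases the ratio is 0.883 or 0.946, worth about 28% or 12% more participants (1/0.883² = 1.28; 1/0.946² = 1.12). If baseline and follow-up times correlate at about 0.9, as may happen immediately after one session, the gain is close to nil. The comparison uses one contrast; the planned ANOVA has three evaluations, so its overall group-by-time test is not identical to it.

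It would be too strong to say that the healthy-side baseline will sharpen the comparison at no cost. Its own contribution is a factor of 0.82 to 1.01, it depends on correlations that the documents do not report, and it uses a degree of freedom. The main outcome (pain on arm elevation), the sample size and the main comparison are unaffected.

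**What to change.** In section 5.4.3, state that the functional outcome is the symptomatic-side completion time of each test. Add the functional tests to the assessment list in section 5.4, so that their baseline measurement does not rest on the abstract alone.

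In section 5.7, state that groups are compared on this outcome at each post-exercise evaluation by ANCOVA, adjusting for the symptomatic side's own baseline time, with the healthy-side baseline time as a pre-specified second covariate. Use only the baseline healthy-side value, since later ones are affected by treatment. Do not use it in place of the own baseline: as the only covariate it can do worse than the planned contrast (SE ratio 1.13 at an own-baseline correlation of 0.7 and a healthy-side correlation of 0.5). Say what replaces Friedman for this outcome if the times are skewed, for example the same model on log time.

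The cost is a few sentences and one degree of freedom per covariate. The planned software fits this model, and no new data are needed.

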### 5.5 Intervention Protocol

Individuals from each group will perform an exercise session according to their group (isometric and isotonic) on the day of baseline assessment in order to verify the immediate effects of exercises. Then, they will participate in a six-week intervention, twice a week, in order to verify the effects of a strengthening program directed at the RC. Exercises will be performed on both limbs.

Individuals from all groups will undergo a protocol for stretching and strengthening the periscapular musculature following the protocol used by Camargo et al (53), which consists of stretching the upper trapezius and pectoralis minor muscles and the posterior portion of the shoulder, and strengthening the serratus anterior and lower trapezius muscles.

The evaluation to determine the initial loads of the exercises will be carried out one week before the baseline evaluation and beginning of the interventions. At that moment, participants will also familiarize themselves with each exercise with light resistance and will be guided by the evaluator to perform the technique correctly. In order to adjust and progress the exercise load over the six weeks of intervention, the assessments will be repeated in the third and fifth weeks of intervention, as shown in Figure 2 with the flowchart of the intervention procedures and progression of each group.

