#### *5.5.2 Isometric Exercise Group*

Isometric exercises for RC muscles will consist of 3 repetitions of 32 seconds at an intensity of 70% of the maximum isometric strength for each exercise, according to the protocol adapted from Rio et al. (27,28), and with an interval between repetitions of 80 seconds (26). The evaluation of maximum strength as well as the performance of the exercises will be performed with a manual dynamometer coupled to a rigid bulkhead and attached to a fixed wooden column. The dynamometer has a function which allows real-time monitoring of the developed force, allowing a visual feedback that will show the individuals the maintenance of the determined load during the exercise.

The determination of maximum isometric strength for the supraspinatus and internal and external rotator muscles will be performed during the shoulder strength assessment described above. The positioning of the individuals to perform the isometric exercises for these muscle groups will be the same as in the evaluation. Elevation of the shoulder in the plane of the scapula at 90° was adopted because it presents a lower risk of compression of the supraspinatus in the coracoacromial arch and, consequently, generates less pain and additional

injuries than exercises at lower arm elevation angles (55). The elevation movement should be performed with the thumb facing upwards, as the supraspinatus muscle is more selective compared to the middle and posterior deltoids (56).

In order to carry out the exercises, the individuals will be instructed to push the dynamometer in the direction of the desired movement and follow the sound feedback of the equipment, pre-adjusted to 70% of the maximum force, and the researcher responsible for the training will give verbal feedback so that the individuals avoid change of positioning or compensation and to avoid excessive contraction of the upper trapezius during the supraspinatus exercise.

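### Sections 5.4 and 5.5 contradict each other on the blind evaluator: as written, the evaluator coaches group-specific exercises after allocation, so blinding is lost before baseline unless a separate unblinded person does this work

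*Combined protocol and SAP*

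**What the plan says.** Section 5.4 (Evaluation procedures) sets out the masking: "All evaluations will be carried out by an evaluator who will not know which intervention group the individuals belong to", "with the interventions applied by two other trained researchers". It also fixes the order of events. "One week before the initial assessment, individuals will be randomly allocated using the online randomization tool". Once the group is known, participants are shown the evaluation equipment, and "individuals allocated to the isometric or isotonic exercise group will perform the initial load determination test for each of the exercises". The same section has the allocation carried out by one of the people applying the intervention, and says that nobody else knows the group.

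Section 5.5 (Intervention Protocol) places the load determination one week before baseline. Of that same visit it says that "participants will also familiarize themselves with each exercise with light resistance and will be guided by the evaluator to perform the technique correctly". It adds that "the assessments will be repeated in the third and fifth weeks of intervention", without naming who does this.

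Section 5.5.2 describes the isometric work as timed holds against a fixed dynamometer. The maximum that sets the load "will be performed during the shoulder strength assessment described above". Section 5.5.3 describes the isotonic work as concentric and eccentric dumbbell exercise at 8 RM.

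**The concern.** The evaluator is described as blind in one section and as exercise coach in the next, at a visit where the tests depend on the allocated group. Anyone who corrects a participant's technique in these exercises sees which programme it is.

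The arms are openly different and the protocol describes no masking of participants, so the evaluator is the only masked party. Several outcomes pass through that person's hands:

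- Participants are asked for a 0–10 pain rating after the tests (section 5.4.2). The sample size in section 5.2 rests on pain on that scale during unloaded arm elevation.
- Maximal contractions are made with verbal encouragement (section 5.4.2).
- Functional tasks are timed by stopwatch (section 5.4.3).

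Section 4 states a directional hypothesis in favour of isometric exercise. An evaluator who knows the group therefore also knows which result is expected. Blinding lost at the outset cannot be restored in the analysis.

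**Working it through.** **Setting the sections side by side**

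1. Allocation: one week before the initial assessment (5.4).
2. Load tests: after allocation, for the exercises of the allocated group (5.4), and one week before baseline (5.5). This is the same visit or immediately adjacent to it.
3. Familiarisation: at the time of the load tests, covering each exercise, with technique guided by the evaluator (5.5).
4. Can the exercises be told apart? Yes: dynamometer holds (5.5.2) against dumbbell repetitions (5.5.3).
5. Who is the evaluator? The only outcome evaluator the protocol introduces is the blind one (5.4). Treatment staff are called researchers in 5.4, and 5.5.2 uses the same word for the person supervising training.
6. Is there a way out in the text? It does not say that the evaluator in 5.5 is another person, that every participant practises both programmes, or that the evaluator coaches only the periscapular exercises shared by both groups.

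Steps 1 to 5 together mean that the evaluator, if the same person throughout, knows the arm before the baseline assessment. That contradicts 5.4.

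**Sensitivity of the pain comparison (illustration)**

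The plan gives no figure for bias, so there is none to reproduce. Inputs from section 5.2: SD 2.30, 21 per group, α = 0.05. Assumed, not from the documents: a differential shift *b* in the group difference when there is no true effect.

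- Standard error of the difference: SD × √(2/n) = 2.30 × √(2/21) = 0.710 points.
- Two-sided t-test with 21 + 21 − 2 = 40 degrees of freedom: critical value 2.021.
- Rejection probability from the noncentral t distribution with noncentrality *b*/0.710:

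| Assumed shift *b* (points) | *b*/SE | False-positive rate |
|---|---|---|
| 0 | 0 | 5.0% |
| 0.25 | 0.35 | 6.4% |
| 0.5 | 0.70 | 10.6% |
| 1.0 | 1.41 | 28.0% |

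**The case against.** The strongest reply is that the evaluator in 5.5 need not be the evaluator in 5.4. The word comes shortly after a sentence about the evaluation of initial loads, inside the intervention section, so it may simply mean whoever runs that load test. The statement in 5.4 that only an intervention researcher knows the group fits this reading. In addition, 5.4 and 5.5 refer to Figures 1 and 2, which were not available in the text reviewed and might identify the staff. This stands as far as intent goes: actual loss of blinding is not shown. It does not remove the defect, because the readable text directs the evaluator to coach, and the same edit is needed whichever meaning was intended.

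Three stronger readings are tempting, and the documents do not support them:

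- *The isometric maximum in 5.5.2 unblinds the evaluator.* It does not by itself. All participants in both arms do that strength test, and a trainer can work out the training load from the value afterwards.
- *The evaluator is exposed again in weeks 3 and 5.* Section 5.5 names nobody for those assessments. This is a gap to fill, not a second contradiction.
- *A blind evaluator would remove the bias in pain, or the false-positive rates above measure this defect.* Pain ratings and the two questionnaires come from participants who know their exercise, and that reporting bias stays whoever asks. The shifts are assumed and do not separate evaluator bias from participant expectation. They also use a simple t-test, not the repeated-measures ANOVA of section 5.7. A shift of 0.1 points would give about 5.2%, so a small bias would matter little.

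**Conclusion.** The concern holds as a contradiction in the text. Sections 5.4 and 5.5 cannot both be followed if the evaluator is one person, and evaluator blinding is then lost before baseline. It survives only if a separate unblinded person does the load tests and coaching, which the protocol does not say. What is exposed is the part of the outcomes that the evaluator can influence: the asking of pain, encouragement in maximal contractions, and hand timing.

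The size of any resulting bias is unknown. For assumed shifts from 0.25 to 1.0 points, the false-positive rate for pain would run from about 6% to 28%. This shows how sensitive a trial with a standard error of 0.71 points is, and does not predict the bias. The point deserves correction before enrolment because this is the only masking claimed and the remedy costs almost nothing.

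**What to change.** - In 5.5, replace 'the evaluator' with 'one of the two intervention researchers' for familiarisation and the initial load tests.
- In 5.5, name the same staff for the week 3 and week 5 load assessments.
- State that all of these take place without the outcome evaluator present.
- Bring 5.4 into line: if both intervention researchers carry out group-specific work, both will know the group, so the statement that only one person knows it needs rewording.
- Reconcile 5.5.2 with 5.4 by stating who uses the strength-assessment values to set the training load. Masking requires no additional strength test and no change in how the load is set.
- Ask participants not to mention their exercises at evaluations.
- Optionally, record the evaluator's guess of group at six weeks, so that the success of blinding can be reported.

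The cost is a few sentences and a clear division of tasks among staff the trial already has, with no extra visit or personnel.
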